#### **6.6 COVID-19 CONCURRENT INFECTION MANAGEMENT PLAN**

If a participant on the study is diagnosed as asymptotically positive for COVID-19, their management will continue unchanged on the study. This means that they will continue to take their IMP, unless the clinical circumstances change. Study visits will be delayed as necessary if there is a risk of transmission from an asymptomatic participant. Transmission risk will be assessed by a clinician on the study

Patients who are symptomatic and test positive for COVID-19, or who are symptomatic and are clinically assessed to have probable COVID-19 in the absence of a positive test, will be managed on a case-by-case basis according to clinical assessment with consideration of the current recommendations at the time. This may require the use of open-labelled prednisolone or hydrocortisone, meaning the temporary cessation of study IMP. Once the participant has clinically improved, the IMP will be restarted with a doubling regimen if deemed necessary. Remaining visits may be delayed accordingly, if the infection occurs close to a study Visit. Protocol deviation forms will be completed in these circumstances.

Emergency treatment is unchanged. Decisions on COVID-19 management will be made clinically on a case-by-case basis in accordance with the guidance above. The final decision in all cases will be made by the Chief Investigator.

## 7. PHARMACOVIGILANCE

### 7.1 DEFINITIONS

**Adverse Event (AE):** any untoward medical occurrence in a patient or clinical trial subject administered a medicinal product and which does not necessarily have a causal relationship with this treatment. An AE can therefore be any unfavourable and unintended sign (including an abnormal laboratory finding), symptom, or disease temporally associated with the use of an investigational medicinal product (IMP), whether or not considered related to the IMP.

**Adverse Reaction (AR):** all untoward and unintended responses to an IMP related to any dose administered. All AEs judged by either the reporting investigator or the sponsor as having reasonable causal relationship to a medicinal product qualify as adverse reactions. The expression reasonable causal relationship means to convey in general that there is evidence or argument to suggest a causal relationship.

**Unexpected Adverse Reaction:** an AR, the nature or severity of which is not consistent with the applicable product information (e.g. investigator's brochure for an unapproved investigational product or summary of product characteristics (SmPC) for an authorised product). When the outcome of the adverse reaction is not consistent with the applicable product information this adverse reaction should be considered as unexpected. Side effects documented in the SmPC which occur in a more severe form than anticipated are also considered to be unexpected.

**Serious Adverse Event (SAE) or Serious Adverse Reaction:** any untoward medical occurrence or effect that at any dose:

- **Results in death.**
- **Is life-threatening** – refers to an event in which the subject was at risk of death at the time of the event; it does not refer to an event which hypothetically might have caused death if it were more severe.

- **Requires hospitalisation, or prolongation of existing inpatients' hospitalisation.**
- **Results in persistent or significant disability or incapacity.**
- **Is a congenital anomaly or birth defect.**

Medical judgement should be exercised in deciding whether an AE/AR is serious in other situations. Important AE/ARs that are not immediately life-threatening or do not result in death or hospitalisation but may jeopardise the subject or may require intervention to prevent one of the other outcomes listed in the definition above, should also be considered serious.

**Suspected Unexpected Serious Adverse Reaction (SUSAR):** any suspected adverse reaction related to an IMP that is both unexpected and serious.

## 7.2 CAUSALITY

Most adverse events and adverse drug reactions that occur in this study, whether they are serious or not, will be expected treatment-related toxicities due to the drugs used in this study. The assignment of the causality should be made by the investigator responsible for the care of the participant using the definitions in the table below.

If any doubt about the causality exists, the local investigator should inform the study coordination centre who will notify the Chief Investigators. The pharmaceutical companies and/or other clinicians may be asked to advise in some cases.

In the case of discrepant views on causality between the investigator and others, all parties will discuss the case. In the event that no agreement is made, the MHRA will be informed of both points of view.

| Relationship          | Description                                                                                                                                                                                                                                                                                                         |
|-----------------------|---------------------------------------------------------------------------------------------------------------------------------------------------------------------------------------------------------------------------------------------------------------------------------------------------------------------|
| Unrelated      | There is no evidence of any causal relationship                                                                                                                                                                                                                                                                     |
| Unlikely       | There is little evidence to suggest there is a causal relationship (e.g. the event did not occur within a reasonable time after administration of the trial medication). There is another reasonable explanation for the event (e.g. the participant's clinical condition, other concomitant treatment).            |
| Possible       | There is some evidence to suggest a causal relationship (e.g. because the event occurs within a reasonable time after administration of the trial medication). However, the influence of other factors may have contributed to the event (e.g. the participant's clinical condition, other concomitant treatments). |
| Probable       | There is evidence to suggest a causal relationship and the influence of other factors is unlikely.                                                                                                                                                                                                                  |
| Definitely     | There is clear evidence to suggest a causal relationship and other possible contributing factors can be ruled out.                                                                                                                                                                                                  |
| Not assessable | There is insufficient or incomplete evidence to make a clinical judgement of the causal relationship.                                                                                                                                                                                                               |

## 7.3 REPORTING PROCEDURES

All adverse events should be reported. Depending on the nature of the event the reporting procedures below should be followed. Any questions concerning adverse event reporting should be directed to the study coordination centre in the first instance. A flowchart is given below to aid in the reporting procedures.

### **7.3.1 Non-serious AR/AEs**

All such toxicities, whether expected or not, should be recorded in the toxicity section of the relevant case report form and sent to the study coordination centre within one month of the form being due.

### **7.3.2 Serious AR/AEs**

All SAEs and SUSARs should be reported on the day that the local site is aware of the event. The SAE form asks for nature of event, date of onset, severity, corrective therapies given, outcome and causality (i.e. unrelated, unlikely, possible, probably, definitely). The responsible investigator should sign the causality of the event. Additional information should be sent within 5 days if the reaction has not resolved at the time of reporting.

#### **SAEs**

An SAE form should be completed and faxed or emailed to the study coordination centre and sponsor for all SAEs within 24 hours. However, relapse and death due to adrenal insufficiency, and hospitalisations for elective treatment of a pre-existing condition do not need reporting as SAEs.

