As participants will be changing their steroid treatment as part of this study, there is a risk of undertreatment. This risk will be minimised as patients will be trialled on the new regimen if they have not previously received it before. Possible symptoms will include tiredness, dizziness, pre-syncope, syncope, palpitations, and abdominal pain. These will be detected through symptom reporting, which will take place during all visits and telephone consultations. Participants will also have a 24-hour emergency contact number for a study clinician which they will be instructed to call if they feel unwell.

At times of intercurrent illness, participants will be asked to double the tablets that they are taking. This is usual clinical practice and will be overseen by a study clinician, who will be available on a 24-hour emergency contact number. Specifically, participants will be asked to take an additional tablet from their morning bottle for the first double dose, before doubling the number of tablets that they usually take from each bottle thereafter. Therefore, instead of taking one tablet from the morning, noon and afternoon bottles, participants will take two from each bottle at the allocated time after the special arrangement for the first double dose.

The only procedure being undertaken as part of this study is venepuncture, thus there may be slight pain when this is performed. Efforts will be made to minimise the frequency and quantity of blood taken

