## 8.2 TRIAL CLOSURE

The end of the study is defined as the completion of the last visit for the last participant. Once all queries are resolved the study will then be locked, unblinded and will enter a data analysis phase, before final closure of the study. This is anticipated to take 6 months.

The Chief Investigator will notify the sponsor the trial has ended. The REC and MHRA will be informed that the study has been concluded within 90 days (or 15 days in the case of a premature closure of the study).

All remaining IMPs will be disposed of by the ICHNT pharmacy or returned to Activase Pharmaceuticals Ltd, after accountability and inventory has been checked by the trial monitor. Authorisation should be sought from the sponsor or CI prior to disposal or return of the IMP.

When the study has been closed, the participants will be unblinded and the data analysis phase will begin. Code-break envelopes will be retrieved from all holders.

The trial will be halted prematurely if a particular statistically significant serious adverse event in more than three individuals upon review by the chief investigator or DMC is deemed to be related to either one of the study medications, and not the medical condition itself.

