### 8.3 SAFETY VARIABLES

The safety variables measured in this study are included as part of the secondary efficacy variable and are reproduced below:

- Safety
  - assessed by reporting of symptoms of steroid deficiency and myopathy and review of routine monitoring blood tests including full blood count (FBC), renal profile, liver function tests (LFTs), creatine kinase (CK), Adrenocorticotrophic hormone (ACTH) cortisol binding globulin (CBG) and bicarbonate.

In addition, the number of adverse events (AE), serious adverse events (SAE), and SUSARs (suspected unexpected serious adverse reactions) will be recorded for each Study Period.

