### 9.6.6 SAFETY

**Outcome definition:** Treatment arm difference in i) FBC, ii) renal profile, iii) LFTs, iv) CK, v) ACTH, vi) CBG, vii) Bicarbonate viii) number of reports of myopathic symptoms, or nausea; from baseline to Day 120.

**Analysis:** A multilevel repeated measures linear mixed effect model will be used to estimate the treatment arm difference in the above safety outcomes (except (viii)), from baseline to Day 120. Similar to the primary analysis model, the model will include fixed effects for time (2 categories: Day 30 and Day 120), treatment arm (2 categories: prednisolone and hydrocortisone), period, type of AI (primary or secondary), baseline outcome. A random participant effect will be included and an unstructured covariance matrix will be used. The treatment effect at 120 days will be reported as a p-value with a 95% confidence interval. The models assumptions about random effects distributions, correlation structure and residuals will all be investigated. If any assumptions are poorly met then log transformation of the analyte in question, will be explored. If the mixed effect model including both 30 and 120 day outcomes fails to converge, treatment effects will be estimated using separate mixed linear regression models for each follow-up time point.

Data for symptom reporting will tabulated according frequency of reported symptoms will be presented at baseline and Day 120 for each treatment arm. McNemar's test will be used to assess the change between time periods.

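### Protocol 7.3.2 exempts death and undefined relapse due to adrenal insufficiency from SAE reporting, against the protocol's own SAE definition and with no crisis or death count in the SAP to replace it

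*Combined protocol and SAP*

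**What the plan says.** Protocol 7.1 makes an event serious if, among other criteria, it "Results in death", is life-threatening, or "Requires hospitalisation, or prolongation of existing inpatients' hospitalisation". Protocol 7.3.2 requires a form for every SAE within 24 hours and puts the investigator's signed causality judgement on that form. Its SAE paragraph then states: "However, relapse and death due to adrenal insufficiency, and hospitalisations for elective treatment of a pre-existing condition do not need reporting as SAEs".

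On the harm to be expected, Protocol 1.2 says: "As participants will be changing their steroid treatment as part of this study, there is a risk of undertreatment". Protocol 1.1 describes Addisonian crisis as a life-threatening result of under-replacement, and the SAP introduction calls it potentially fatal.

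SAP 8.3 records numbers of AEs, SAEs and SUSARs for each study period. SAP 9.7 tabulates adverse events by treatment and period and lists SAEs individually. SAP 8.3 describes safety as "assessed by reporting of symptoms of steroid deficiency and myopathy", together with routine blood tests. In SAP 9.6.6 the only symptom outcome is the "number of reports of myopathic symptoms, or nausea".

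The halting rule in Protocol 8.2 concerns a serious adverse event in more than three individuals that "is deemed to be related to either one of the study medications, and not the medical condition itself".

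**The concern.** Every participant needs steroid replacement, and the trial changes how it is given. If a study regimen under-replaces someone, the serious consequence is decompensated adrenal insufficiency. An investigator can truthfully describe that event as due to adrenal insufficiency, and the exemption then applies, even if the study regimen was the reason. The step that would separate disease from drug failure, the signed causality judgement on the SAE form, falls away with the form.

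An exemption of this kind can be defended when the event is captured as a trial endpoint. Here the primary outcome is osteocalcin, and no secondary outcome counts crises or deaths. What is at stake is whether the DMC, at its 6-monthly reviews, and the final report would recognise a crisis or death on either drug as a serious event.

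**Working it through.** The plan states no figure on this point, so the check follows an event through the text. An illustration of size comes after it.

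**Tracing a crisis or death attributed to adrenal insufficiency**

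1. *Definition (Protocol 7.1).* A death is serious. So is a life-threatening crisis or an unplanned admission for one.
2. *SAE form (Protocol 7.3.2).* The death is exempt by name. The crisis is exempt if it is read as a relapse, a term the protocol does not define. Only elective admissions are exempted by name, so an emergency admission could be read either way. No clause restores reporting for events on, or related to, study drug.
3. *SUSAR route (Protocol 7.3.2).* This has no exemption, but it needs the event to be suspected of a drug cause and to be unexpected. Protocol 7.5 already names acute adrenal insufficiency and death, though only after too rapid a dose reduction. It also says that the listed prednisolone effects are not expected at the doses used here. Expectedness is therefore arguable.
4. *General AE route (Protocol 7.3 and 7.3.1).* Section 7.3 says that all adverse events are to be reported. The case report form route is in 7.3.1, whose heading restricts it to non-serious events and which allows a month. A serious but exempted event has no explicit route.
5. *SAP counts (8.3 and 9.7).* An event not reported as an SAE would not enter the SAE count or the individual listing. If recorded as an AE, it would be one entry in a table by treatment and period. The SAP text specifies no row for crises or deaths.
6. *Halting rule (Protocol 8.2).* The rule counts serious adverse events. An event that never arrives as one could be missed.

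**Symptoms, a secondary point**

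Protocol 1.2 lists tiredness, dizziness, pre-syncope, syncope, palpitations and abdominal pain as possible symptoms of undertreatment. None is in SAP 9.6.6(viii), although SAP 8.3 covers steroid-deficiency symptoms. Nausea, which Protocol 1.1 names as a symptom of under-replacement, is in 9.6.6(viii).

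**Illustration of size**

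Inputs: 55 recruited and 44 completers (Protocol 9); blinded drug from Day 2 to Day 120, which is 119 days per period (Protocol 8). The documents give no crisis rate, so 2 to 10 per 100 patient-years is assumed.

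- Exposure per drug = participants × 119 / 365.25.
  - 44 completers: 44 × 119 / 365.25 = 14.3 patient-years.
  - All 55: 55 × 119 / 365.25 = 17.9 patient-years.
- Expected crises per drug = rate × exposure.
  - Lowest: 0.02 × 14.3 = 0.3.
  - Highest: 0.10 × 17.9 = 1.8.
- Chance of at least one crisis on either drug, if events are independent at a constant rate = 1 − exp(−rate × 2 × exposure).
  - Lowest: 1 − exp(−0.02 × 28.7) = 44%.
  - Highest: 1 − exp(−0.10 × 35.8) = 97%.

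**The case against.** The strongest reply is that the exemption concerns only reporting as an SAE. All adverse events are still to be reported. AE reporting is scheduled at the study visits and telephone consultations. AEs are tabulated by events and by participants, and the DMC's remit is the safety data rather than SAEs alone. This stands. A reader might infer that the main harm of switching would be missing from the trial's safety data or never counted, and the documents do not support that. What remains is that a serious exempted event has no explicit form and no line of its own in the analysis.

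A reader might also infer that every crisis would count as zero SAEs. That goes too far for crises, because relapse is undefined, Protocol 7.1 still classes these events as serious, and SAP 9.7 promises a listing of all SAEs. The exemption of deaths is explicit. For crises the fault is ambiguity and internal conflict.

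Third, the halting rule might seem to discount these events by setting aside those due to the condition. Its wording asks for a causality judgement, and a crisis judged to be caused by study drug would still qualify. The weakness lies earlier, in whether the event is reported as serious at all.

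Finally, so few events cannot support a comparison between the drugs even with full reporting, and SAP 9.7 plans description only. That is right. The point rests on the text, and the arithmetic only shows how few events there would be to lose.

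**Conclusion.** The concern holds as a defect in safety reporting. Protocol 7.3.2 contradicts Protocol 7.1 and, without qualification, exempts death and undefined relapse due to adrenal insufficiency. Those are the severe outcomes of a risk that the protocol itself foresees. Followed as written, the rule gives incomplete 24-hour reports, SAE counts and SAE listing, omits the signed causality assessment, and could leave the halting rule short of events. General AE reporting and the SUSAR route lessen the damage without closing the gap.

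The 0.3 to 1.8 expected crises per drug depend wholly on the assumed rate and are illustrative. The conclusion does not depend on them. The mismatch between SAP 9.6.6(viii) and SAP 8.3 is real but secondary. Sample size, significance level and primary analysis are unaffected. Because oversight of participant safety is involved and the remedy is small, the correction should be made.

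**What to change.** 1. In Protocol 7.3.2, delete relapse and death due to adrenal insufficiency from the exemption, so that these events are reported as SAEs, receive a signed causality assessment and reach the DMC. The exemption for elective admissions can stay.
2. In SAP 9.7, add a table of adrenal crises, related unplanned admissions and deaths by drug and period, as events and as participants.
3. As a secondary change, bring SAP 9.6.6(viii) into line with SAP 8.3 by adding the deficiency symptoms listed in Protocol 1.2, while keeping nausea and myopathic symptoms. Substituting the Protocol 1.2 list for the present wording would lose nausea, which that list omits.

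The cost is a one-sentence protocol amendment, SAP wording and a few more SAE forms. The information already arises at scheduled visits and calls.

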#### **SUSARs**

In the case of suspected unexpected serious adverse reactions, the staff at the site should:

Complete the SAE case report form & send it immediately (within 24 hours, preferably by fax), signed and dated to the study coordination centre and sponsor together with relevant treatment forms and anonymised copies of all relevant investigations.

**Or**

Contact the study coordination centre by phone and then send the completed SAE form to the study coordination centre and sponsor within the following 24 hours as above.

The study coordination centre will notify the MHRA, REC and the Sponsor of all SUSARs occurring during the study according to the following timelines; fatal and life-threatening within 7 days of notification and non-life threatening within 15 days. All investigators will be informed of all SUSARs occurring throughout the study.

Local investigators should report any SUSARs and /or SAEs as required by their Local Research Ethics Committee and/or Research & Development Office.

## **7.4 REFERENCE SAFETY INFORMATION FOR HYDROCORTISONE**

### **Undesirable effects:**

*Blood and Lymphatic System Disorders:* Leucocytosis

*Immune System Disorders:* Hypersensitivity.

*Endocrine Disorders:* Increased or decreased motility and number of spermatozoa, menstrual irregularities, amenorrhoea, development of Cushingoid state, suppression of growth in children, secondary adrenocortical and pituitary unresponsiveness (particularly in times of stress, as in trauma, surgery, or illness), decreased carbohydrate tolerance, manifestations of latent diabetes mellitus, hyperglycaemia, increased requirements for insulin or oral hypoglycaemic agents in diabetes, hirsutism.

*Metabolism & Nutrition Disorders:* Sodium retention, fluid retention, potassium loss, hypokalaemic alkalosis, increased calcium excretion, negative nitrogen balance due to protein catabolism, weight gain, increased appetite.

*Psychiatric Disorders:* psychic disturbances, psychological dependence, insomnia. A wide range of psychiatric reactions including affective disorders (such as irritable, euphoric, depressed and labile mood, and suicidal thoughts), psychotic reactions (including mania, delusions, hallucinations and aggravation of schizophrenia), behavioural disturbances, irritability, anxiety, sleep disturbances, and cognitive dysfunction including confusion and amnesia have been reported. Reactions are common and may occur in both adults and children. In adults, the frequency of severe reactions has been estimated to be 5-6%. Psychological effects have been reported on withdrawal of corticosteroids; the frequency is unknown.

*Nervous System Disorders:* Convulsions, increased intracranial pressure with papilloedema (pseudotumour cerebri) usually after treatment, vertigo, headache, malaise.

*Eye disorders:* Posterior subcapsular cataracts, increased intra-ocular pressure, papilloedema, corneal or scleral thinning, exacerbation of ophthalmic viral disease, glaucoma, exophthalmos.

*Gastro-intestinal Disorders:* Peptic ulcer with possible perforation and haemorrhage, perforation of the small and large bowel particularly in patients with inflammatory bowel disease, pancreatitis, abdominal distension, ulcerative oesophagitis, dyspepsia, oesophageal candidiasis, nausea.

*Skin and Subcutaneous Tissue Disorders:* Impaired wound healing, thin fragile skin, petechiae, and ecchymoses, erythema, striae, telangiectasia, acne, increased sweating, may suppress reactions to skin tests, other cutaneous reactions such as allergic dermatitis, urticaria, angioneurotic oedema

*Musculoskeletal, Connective Tissue & Bone Disorders:* Muscle weakness, steroid myopathy, loss of muscle mass, osteoporosis (especially in postmenopausal females), vertebral compression fractures, aseptic necrosis of femoral and humeral heads, pathological fracture of long bones, tendon rupture.

*Cardiac Disorders:* Myocardial rupture following recent myocardial infarction, congestive heart failure in susceptible patients,

*Vascular Disorders:* thrombo-embolism, hypertension,

*Respiratory, Thoracic & Mediastinal Disorders:* Hiccups.

*Other:* Hypersensitivity, leucocytosis, weight gain, increased appetite, nausea, malaise.

